|                                         | 0%                                        | 0%                        | 0%                        | 0%                        | 50%                       | 0.49                        |
| Based on 2000 simulations for each row. |                                           |                           |                           |                           |                           |                             |

When the true residual CV is 20%, there is reasonable power to detect a dose response for either endpoint when the true increase is at least 20-30% in two or more cohorts. There is limited power to detect a dose response when the effect is only in the highest cohort. Also, when the true residual CV is larger, the power reduces substantially. To reduce residual variability, the fitted model will also adjust for the baseline  $\text{PaO}_2/\text{FiO}_2$  ratio or Ventilation Index as a proxy measure of baseline severity. Significant dose response model fits can be utilized to estimate doses that provide clinically meaningful results and aid in planning for future studies.

Efficacy data will be continuously reviewed after each cohort to assess whether results are compelling enough to suggest initiation of a larger randomised controlled clinical trial. Interim efficacy data will be analysed using a simple Bayesian adaptive approach. After each cohort completes dosing plus 24 hours of follow-up, the posterior distributions of the mean change in  $\text{PaO}_2/\text{FiO}_2$  ratio and the mean change in Ventilation Index will be determined under an assumed normal distribution with a non-informative prior. The change in  $\text{PaO}_2/\text{FiO}_2$  and change in Ventilation Index and may be transformed for analysis (e.g., log transformed) to better satisfy normality assumptions. Interim efficacy will be declared for the purposes of further trial planning if there is relatively high posterior probability (e.g., > 80%) that EITHER the true mean change in  $\text{PaO}_2/\text{FiO}_2$  OR mean change in Ventilation Index at 24 hours after last administration of surfactant “high” (e.g.,  $\geq 20\%$ ), either for an individual cohort or for all treated patients combined.

The following table shows the probability of observing at least 80% posterior probability that the true improvement is  $\geq 20\%$  on average for each endpoint.

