|                                       |                                                                                                                 |
|---------------------------------------|-----------------------------------------------------------------------------------------------------------------|
| Relative change from baseline in each | Cumulative probability to observe at least 80% posterior probability that true change is $\geq 20\%$ on average |
|---------------------------------------|-----------------------------------------------------------------------------------------------------------------|

| group, on average                               | After 6 complete | After 9 complete | After 12 complete |
|-------------------------------------------------|------------------|------------------|-------------------|
| 0%                                              | 0.01             | 0.02             | 0.03              |
| 10%                                             | 0.06             | 0.14             | 0.19              |
| 20%                                             | 0.30             | 0.46             | 0.58              |
| 25%                                             | 0.45             | 0.64             | 0.75              |
| 30%                                             | 0.60             | 0.81             | 0.90              |
| 1000 simulations per row, assumes true CV = 20% |                  |                  |                   |

When there is no true improvement, there is < 5% probability to declare efficacy at an interim time point. When the true improvement is 30% on average, there is 60% (81%) probability to declare efficacy at an interim time point after 6 (9) patients complete the study.

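### The interim efficacy rule has no baseline covariate although the final model does, yet its operating table assumes the same 20% CV that the protocol calls residual for the final model

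*Protocol*

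**What the plan says.** All of this stands in Protocol section 10, Efficacy.

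- **Final model.** "To reduce residual variability, the fitted model will also adjust for the baseline" PaO2/FiO2 ratio or Ventilation Index, as a proxy for baseline severity. The power discussion is worded accordingly: "When the true residual CV is 20%, there is reasonable power to detect a dose response for either endpoint".
- **Interim rule.** After each cohort, for each endpoint, "the mean change in Ventilation Index will be determined under an assumed normal distribution with a non-informative prior". No covariate is named. The change "may be transformed for analysis (e.g., log transformed) to better satisfy normality assumptions".
- **Declaration.** "Interim efficacy will be declared for the purposes of further trial planning if there is relatively high posterior probability (e.g., > 80" per cent) that the true mean change is at least 20%, "either for an individual cohort or for all treated patients combined". Under section 4 a cohort is 3 treated patients and 2 controls, so the smallest group tested is 3.
- **Operating characteristics.** The table footnote reads "1000 simulations per row, assumes true CV = 20" per cent. With no true effect the printed values are 0.01, 0.02 and 0.03 after 6, 9 and 12 patients, summarised as: "When there is no true improvement, there is < 5% probability to declare efficacy at an interim time point".

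**The concern.** The protocol's reason for adjusting the final model is that baseline explains part of the variability in change. If so, a rule without the covariate faces a larger CV than the adjusted model. Yet 20% serves both: as the *residual* CV beside the power table and as the *true* CV under the interim table. Unless baseline explains nothing, these cannot be the same quantity.

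There is also a conditional effect. If change depends on baseline, a cohort of 3 whose baselines happen to be unfavourable (low for PaO2/FiO2; high for the Ventilation Index, where section 3.1 makes benefit a reduction) drifts toward apparent improvement without any drug effect. The unadjusted posterior cannot separate this from response.

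At stake is the reliability of a rule meant to inform whether a larger trial is planned, and whether its stated error bound describes the rule as written.

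**Working it through.** **Inputs from the protocol:** cohorts of 3 treated and 2 controls; posterior above 0.80 that the mean change is at least 20%; latest cohort or all treated pooled; looks at 6, 9 and 12 treated; CV 20%. **Assumed, because the protocol gives no value:** the correlation r between log change and log baseline, taken from 0 to 0.7.

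**Step 1, reproduce the printed table.** Work with the log ratio, SD = √ln(1 + 0.20²) = 0.198 and threshold ln 1.2. Under a flat prior the posterior of the mean is t with n − 1 df. One endpoint, no covariate, no control term, 100,000 simulated trials per row:

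| True change | Printed (6 / 9 / 12) | Recomputed |
|---|---|---|
| 0% | 0.01 / 0.02 / 0.03 | 0.011 / 0.021 / 0.031 |
| 10% | 0.06 / 0.14 / 0.19 | 0.077 / 0.136 / 0.189 |
| 20% | 0.30 / 0.46 / 0.58 | 0.292 / 0.447 / 0.563 |
| 25% | 0.45 / 0.64 / 0.75 | 0.455 / 0.642 / 0.760 |
| 30% | 0.60 / 0.81 / 0.90 | 0.622 / 0.802 / 0.893 |

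Fourteen of 15 cells agree within 0.02. The other (0.622 against 0.60) is within the error of 1000 simulations (standard error about 0.015). So the table describes an unadjusted rule whose whole variability is 20%.

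**Step 2, if 20% is the residual CV.** The unadjusted log SD is 0.198/√(1 − r²). At r = 0.5 this is 0.198/0.866 = 0.229, and CV = √(exp(0.229²) − 1) = 23%. The adjusted rule below fits a common slope and SD within groups (each treated cohort and the controls), using everyone to date, and reads means at the overall mean baseline.

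| r | Unadjusted CV | False declaration by 12, unadjusted | Adjusted | Detection after 6 at true 30%, unadjusted | Adjusted |
|---|---|---|---|---|---|
| 0 | 20% | 3.1% | 3.0% | 0.62 | 0.61 |
| 0.3 | 21% | 3.9% | 3.2% | 0.61 | 0.61 |
| 0.5 | 23% | 5.4% | 3.6% | 0.58 | 0.60 |
| 0.7 | 28% | 9.1% | 5.0% | 0.53 | 0.59 |

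Repeat runs move the false-declaration figures by about 0.2 points.

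**Step 3, if 20% is the total CV.** The unadjusted rule stays at 0.03 by 12 patients whatever r is. At r = 0.5 the adjusted rule gives 0.02, and detection after 6 patients at a true 30% goes from 0.62 to 0.65.

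**Step 4, one cohort of 3 with an unfavourable mean baseline, no drug effect, total CV 20%.** The spurious log shift is r × 0.198 × d/√3 for a mean baseline d standard errors off.

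- Averaged over all baselines, the cohort passes about 1% of the time.
- r = 0.5, d = 1: 0.5 × 0.198/1.732 = 0.057, a shift of 6%; it passes 1.8% of the time.
- r = 0.5, d = 2: a shift of 12%; it passes about 6%.
- R² = 0.5 (r about 0.71), d = 2: a shift of 18%; it passes about 9%.

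**The case against.** Much of the case on the other side stands.

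- **The CV conflict is an ambiguity, not a proven error.** The footnote says true CV, and the table is reproduced with 20% as the whole variability. On that reading, chance baseline spread is already inside the printed 0.03 and nothing is inflated. A reader might infer that the under-5% statement is wrong. The document does not establish that: it needs the residual reading and an r of about 0.5 or more, and no r is given. At r = 0.3 the rate stays under 5%.
- **A reader might infer that cohorts of three with poor baselines will look like responders.** Step 4 does not bear this out. Even two standard errors off, at least about 91% do not pass. The direction also differs between the endpoints.
- **Each patient is already referenced to their own baseline**, and a log transform is allowed. Only a covariate is missing.
- **Part of the gain in Step 2 comes from pooling the SD, not from the covariate.** Pooled SD without a covariate gives 4.4% at r = 0.5 and 7.8% at r = 0.7, against 5.4% and 9.1% unadjusted and about 3.5% and 5.0% adjusted. So the covariate contributes roughly half the reduction at 0.5 and about two thirds at 0.7. If the pooling is within the two arms rather than within cohorts, every rate is lower (3.3% and 6.4% without the covariate; 2.0% and 3.1% with it), and more than half the reduction at 0.5 is due to pooling. The covariate still adds something in both versions at these correlations.
- **Adjustment does not supply a control comparison.** If both arms improve by 10% or 20% without a drug effect, the treated-only rule declares with probability 0.19 or 0.56 per endpoint by 12 patients. That gap is larger, and this fix leaves it open.
- **The stakes are limited.** The thresholds are given as examples, the declaration serves further trial planning, and it is not among the termination criteria. Section 11.2 refers to a statistical analysis plan that may add detail. However, the protocol itself states the rule and its operating characteristics, so their consistency can be judged here.

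**Conclusion.** The point holds in a limited form. The interim rule leaves out a covariate that the protocol itself expects to reduce variability, and its table uses a 20% CV whose meaning is not fixed.

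- **Residual reading:** 0.03 per endpoint by 12 patients becomes about 0.04, 0.05 or 0.09 at an assumed r of 0.3, 0.5 or 0.7.
- **Total reading:** the printed table stands. The adjusted rule improves it modestly (about 0.03 to 0.02 at r = 0.5, with slightly higher detection), and part of that comes from pooling the SD.
- **Unfavourable baselines:** low PaO2/FiO2 or high Ventilation Index makes a cohort of three modestly more likely to pass falsely, and no more than that.

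These figures assume log-normal changes, a linear relation between log change and log baseline, equal variance across groups, one endpoint, and looks from 6 treated patients as in the printed table.

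**What to change.** 1. State whether the 20% under the interim table is the total CV of the change or the residual CV after baseline adjustment, and use the same term beside the power table.
2. From the second look onward (2 × 5 = 10 randomised patients), compute the interim posterior from a model of the log ratio on log baseline. Estimate slope and residual SD from all treated and control patients to date, with a separate mean for each treated cohort, and read cohort and pooled means at the overall mean baseline. At 10 patients this leaves 10 − 3 group means − 1 slope = 6 df, against 2 df for a cohort of three alone. The first look can stay unadjusted.
3. Re-run the interim table for this rule over a stated range of r, and restate the false-declaration bound from it.

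The cost is analysis wording and one simulation. The baseline values are already recorded under section 7.5. If baseline proves unrelated to change, the loss is about 1 point of detection probability (0.62 to 0.61 after 6 patients at a true 30%).

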**CONTROL:** Each cohort of 3 patients (in the treatment arm) will have 2 patients acting as controls (5 patients per cohort; total control n=8). The protocol for the control arm will be identical to the treatment arm except for surfactant nebulization.

After each cohort has completed treatment (or equivalent time for controls), the investigators will pause to review the outcomes of the treatment based on the co-primary outcomes (PaO2/FiO2 ratio and Ventilation index at 48 hours), reported adverse events and any additional safety or feasibility considerations. Additional trial outcome data may be taken into account if considered important in the opinion of the principal and chief investigators or if requested by the DSMB or TSC.

The decision to progress may be: 1. increase dose to next cohort level according to planned schedule (see below); 2. decrease dose to previous cohort level according to planned schedule (see below); 3. decrease dose to alternative level (specifically for cohort 1); 4. maintain dosage at current level. If there is a substantial and sustained improvement in the outcomes of a cohort, the subsequent cohorts may continue with the same dose as the previous cohort. If no improvement is observed, the subsequent cohort may increase the dosage. Early and substantial improvement during administration of the drug, or adverse events thought to be a safety concern, may prompt the investigators to reduce the administered dose during the conduct of the study.

Decisions relating to trial progression and dose escalation/maintenance/reduction will be made by the TSC after review of data by the DSMB. The DSMB will meet immediately prior to the TSC in open session but may meet in closed session at the request of any members of the DSMB or TSC. The TSC will meet after the DSMB and receive a verbal update from the DSMB. The TSC will be the final arbiter of trial progression and dose escalation/maintenance/reduction decisions. The majority of the TSC and all members of the DSMB will be independent of the trial investigators and trial conduct. An extraordinary meeting of the DSMB may be convened if the investigators have any safety concerns. Such a meeting would make recommendations to the TSC on trial continuation/discontinuation. The trial will not be discontinued on the basis of lack of efficacy. The trial may be stopped early on the basis of safety or feasibility concerns.

[figure not shown]

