## 6 PARTICIPANT ELIGIBILITY CRITERIA

### 6.1 Inclusion criteria

1. Age  $\geq 18$  years old
2. Confirmed COVID-19 positive by PCR
3. Within 24 hours of mechanical ventilation
4. Assent obtained from personnel legal representative (PerLR) or professional legal representative (ProfLR)

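### The interim efficacy rule uses only treated patients' change from their own baseline, so it cannot separate a drug effect from the course under standard care

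*Protocol*

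**What the plan says.** Protocol Section 10, Efficacy, sets a Bayesian interim rule to be applied after each cohort. The quantities are "the posterior distributions of the mean change in" PaO2/FiO2 and in Ventilation Index, which "will be determined under an assumed normal distribution with a non-informative prior". Efficacy is declared, for the purpose of planning further trials, if either mean change is high (20% or more is the example) with high posterior probability (above 80% is the example), "either for an individual cohort or for all treated patients combined".

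The operating characteristics follow in a table whose rows are relative changes from baseline and whose entries are headed "Cumulative probability to observe at least 80% posterior probability that true change is" at least 20% on average. The text below it equates the 0% row with no true improvement and gives a false-declaration probability below 5%. It adds: "When the true improvement is 30% on average, there is 60% (81%) probability to declare efficacy" after 6 (9) patients.

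The trial has concurrent randomised controls. Section 4 states: "Each cohort of 3 patients (in the treatment arm) will have 2 patients acting as controls", for a total of 8. Section 6.1 admits patients "Within 24 hours of mechanical ventilation".

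**The concern.** The rule is defined on a mean change within treated patients. It names no difference from control, although controls are randomised, measured on the same schedule and managed identically apart from the nebulised surfactant.

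Both endpoints can move under ordinary care. PaO2/FiO2 depends on the inspired oxygen setting. The Ventilation Index (Section 3.1) is built from respiratory rate, airway pressures and PaCO2. Patients enter soon after ventilation starts, and Section 10 gives no reason to expect their mean values to stay still over the next two days. In this setting a change from baseline is not the same as a drug effect, yet the table's 0% row and the sentence about a rate below 5% treat them as the same.

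What is at stake is the value of the signal. Section 10 lists quick identification of an efficacy signal, in order to consider a larger randomised trial, among the goals of the study. This rule is the only quantified criterion for that. The error can run in either direction, depending on whether standard-care patients improve or worsen.

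**Working it through.** **Inputs from Section 10 and Section 4.** Threshold 20%; posterior cut-off 80%; CV 20%; tabulated looks after 6, 9 and 12 treated patients; 2 controls per cohort, so 4, 6 and 8 controls at those looks.

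**The rule as a formula.** On the log scale, SD = sqrt(ln 1.04) = 0.198 and the threshold is ln 1.2 = 0.182. With a non-informative prior the posterior of the mean is a t distribution. With n treated patients and mean log change m, declare if

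P = T_(n-1)[(m - 0.182) / (s/√n)] > 0.80,

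for all treated patients pooled or for the current cohort of three. If δ is the drug effect and β the change under standard care, both on the log scale, m estimates δ + β. The rule depends only on that sum.

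**Reproducing the protocol's table.** Treated patients only, one endpoint, cumulative over the three looks, 100,000 runs per row:

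| Mean change from baseline | Protocol: after 6 / 9 / 12 | Recomputed |
|---|---|---|
| 0% | 0.01 / 0.02 / 0.03 | 0.010 / 0.020 / 0.030 |
| 10% | 0.06 / 0.14 / 0.19 | 0.077 / 0.136 / 0.190 |
| 20% | 0.30 / 0.46 / 0.58 | 0.296 / 0.448 / 0.562 |
| 25% | 0.45 / 0.64 / 0.75 | 0.453 / 0.639 / 0.756 |
| 30% | 0.60 / 0.81 / 0.90 | 0.625 / 0.804 / 0.895 |

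Fourteen of the 15 cells agree within 2 points. The remaining cell is 2.5 points off, where the protocol's 1000 simulations have a standard error of about sqrt(0.6 × 0.4/1000) = 1.5 points. Versions that subtract controls (4/6/8, 6/9/12, or 12 at every look) miss by 10 to 29 points at their worst cell. The table was therefore evidently produced without controls.

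**Inert drug, improving background.** Set δ = 0 and read the table at β. The background values are assumed, because the protocol gives none. The probability of a false declaration by 12 treated patients, per endpoint, is 0.03 at 0%, 0.19 at 10%, 0.58 at 20% and 0.75 at 25%.

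**Working drug, worsening background.** Let the drug multiply values by 1.30 while standard care lowers them by 10% or 15% (assumed). The treated change is 1.30 × 0.90 = 1.17 or 1.30 × 0.85 = 1.105. The chance of a declaration by 12 treated patients falls from about 0.90 to roughly 0.4 or 0.2.

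**The same rule on the difference.** Replace m by (treated mean - control mean) and s/√n by s·√(1/n + 1/k) with k controls, keeping the 20% and 80% cut-offs. The background β then cancels. Per endpoint, after 6 / 9 / 12 treated patients:

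| Scenario | Pooled or current cohort | Pooled only |
|---|---|---|
| No drug effect, any common background from 0% to 30% | 0.03 / 0.04 / 0.06 | 0.01 / 0.02 / 0.02 |
| True 30% effect over control | 0.48 / 0.65 / 0.76 | 0.41 / 0.54 / 0.62 |

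In the first column each single cohort is compared with all controls to date. The loss against the protocol's 0.90 comes from the standard error: with 12 treated and 8 controls, √(1/12 + 1/8) = 0.456, against √(1/12) = 0.289 for the treated-only mean.

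**The case against.** The strongest reply is that this is an advisory screen in a small pilot. The declaration serves planning only. The termination criteria in Section 10 contain no stop for benefit, and Section 4 rules out stopping for lack of efficacy. Dose decisions are described elsewhere without reference to this rule. A false signal would lead to consideration of a larger controlled trial, which would test the drug properly. All of this stands, and it limits the severity.

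A reader might infer that the trial ignores its controls. It does not. The final dose-response test has a control group and adjusts for baseline, and the Section 4 review after each cohort allows for an equivalent time for controls. The gap is confined to the interim calculation.

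A reader might also infer that improvement under standard care will trigger the rule. The documents do not show this. The result is a probability that depends on an assumed background, and the only control value in the document is 0%, in the power table. Sections 4 and 5 describe patients whose oxygen needs are rising, and Section 6.1 sets no entry threshold on either endpoint, so regression to the mean cannot simply be presumed. The 20% threshold also absorbs a small drift.

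Larger figures are available but mix in other features. Counting either endpoint (correlation 0.5 assumed) gives 0.32 and 0.75 at a 10% and 20% background, and a look after cohort 1 raises these to about 0.38 and 0.80. Part of that is two-endpoint multiplicity, which lifts even the 0% row to about 0.06 by 12 patients. It is a separate matter and should not be charged to the missing controls.

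One reading might rescue the rule: Section 4 counts five patients per cohort including two controls, so an individual cohort could include them. That does not help, because the quantity is still a mean change and not a difference. Nor is this a detail left to the analysis plan, since the protocol prints both the rule and its operating characteristics.

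**Conclusion.** The concern holds, as a should-fix. The interim rule and its table rest on change from baseline in treated patients alone, and the false-declaration statement below 5% is conditional on no mean change under standard care. The protocol does not state that condition. On the protocol's own figures, a standard-care improvement of 10%, 20% or 25% would give an inert drug a declaration probability of 0.19, 0.58 or 0.75 per endpoint by 12 treated patients. A worsening course would hide a working drug.

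These sizes rest on an assumed background, a CV of 20%, one endpoint and the tabulated looks. The structural point rests on none of them: no choice of threshold or cut-off makes a within-arm change a drug effect. It does not follow that the trial's final conclusions are uncontrolled, or that this rule alone decides whether a larger trial proceeds.

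**What to change.** Base the interim posterior on the treated-minus-control difference in log change from baseline, adjusted for baseline. Make the pooled contrast of all treated patients against all controls to date the main criterion. If single-cohort contrasts are kept, label them as using controls pooled across cohorts, since later cohorts are then compared partly with controls randomised earlier. Comparing each cohort only with its own two controls avoids that, but raises the false-declaration probability to about 0.11 by 12 treated patients when counted beside the pooled contrast.

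Rerun the operating-characteristics table for this difference, under the either-endpoint rule and with the looks actually planned, including the one after cohort 1. Restate the sentences giving the rate below 5% and the 60% (81%) probabilities to match. Show the within-arm change as description only.

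The cost is protocol wording and one simulation; the control data are already collected. The price in sensitivity should be stated openly: at a true 30% effect the chance of a signal by 12 treated patients falls, per endpoint, from 0.90 to about 0.76 (pooled or current cohort) or 0.62 (pooled only). The 0.90 is the chance of detecting a 30% change from any cause, so part of this loss is only apparent.

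### The probabilities quoted for declaring interim efficacy are single-endpoint figures with looks from 6 patients; under the either-endpoint rule the protocol sets, they are higher and under 5% is not assured

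*Protocol*

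**What the plan says.** All of this is in the protocol, section 10, Efficacy, except the cohort size.

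- **When.** The posterior distributions are computed "After each cohort completes dosing plus 24 hours of follow-up". Section 4 gives the cohort size: "Each cohort of 3 patients (in the treatment arm) will have 2 patients acting as controls". With four cohorts, the looks fall after 3, 6, 9 and 12 treated patients.
- **Rule.** "Interim efficacy will be declared for the purposes of further trial planning if there is relatively high posterior probability (e.g., > 80"%) that the mean change is at least 20% in PaO2/FiO2 "OR mean change in Ventilation Index at 24 hours after last administration of surfactant". The test applies "either for an individual cohort or for all treated patients combined".
- **Table.** It is introduced as applying to each endpoint. Its first column is "After 6 complete", and the footnote reads "1000 simulations per row, assumes true CV = 20"%. The row for no change is 0.01, 0.02 and 0.03 after 6, 9 and 12 patients.
- **Text after the table.** "When there is no true improvement, there is < 5% probability to declare efficacy at an interim time point". The next sentence gives 60% (81%) after 6 (9) patients when the true improvement is 30%.

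**The concern.** In this section, declaring efficacy means that either endpoint passes, with a look after every cohort including the first. The two sentences under the table use that term for numbers that describe one endpoint and omit the first cohort's look. A second endpoint and an extra look can only raise the probability of a declaration, whatever the true change.

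Section 10 makes quick detection of an efficacy signal a goal, in order to consider a larger randomised trial. Sections vi and 8.7 have the DSMB make recommendations on starting one. This is the only place where the protocol says how reliable the signal is. A reader would take 0.19 as the chance of a declaration when the true change is 10%, half the 20% target, and would be misled.

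**Working it through.** **Inputs from the protocol.** Cohorts of 3 treated patients, four cohorts; posterior threshold 80%; target change 20%; normal model with non-informative prior, log transform allowed; CV 20% (interim table) and 25% (the alternative in the power table). **Assumed, because the protocol does not give it:** the correlation between the endpoints, taken as 0 to 0.8 for no change and 0 to 0.7 for the other rows.

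**Criterion.** With a non-informative prior, the posterior of a mean from n patients is a t distribution with n − 1 degrees of freedom. A look succeeds if mean − t(0.80, n − 1) × s/√n exceeds the threshold. On the log scale the SD is √ln(1 + 0.20²) = 0.198 and the threshold is ln 1.2 = 0.182.

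**Step 1: reproduce the table.** One endpoint, cohort or pooled, first look after 6, log scale, CV 20%:

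| True change | Stated (6 / 9 / 12) | Simulated |
|---|---|---|
| 0% | 0.01 / 0.02 / 0.03 | 0.011 / 0.021 / 0.031 |
| 10% | 0.06 / 0.14 / 0.19 | 0.078 / 0.135 / 0.190 |
| 20% | 0.30 / 0.46 / 0.58 | 0.291 / 0.446 / 0.562 |
| 25% | 0.45 / 0.64 / 0.75 | 0.456 / 0.641 / 0.758 |
| 30% | 0.60 / 0.81 / 0.90 | 0.623 / 0.803 / 0.893 |

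The largest gap is 0.023, about the noise of 1000 simulations. Adding the look after 3 misses the table by up to 0.10. Using either endpoint misses by 0.11 to 0.31, and pooled-only versions miss by 0.11 or more. So the table is for one endpoint without the first look.

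**Step 2: hand check of the no-change row.** One cohort of 3 passes on one endpoint with probability about 0.0105. Pooled looks add little when there is no change, so with independent looks:

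- one endpoint, 3 cohorts: 1 − 0.9895³ = 0.031 (the table's 0.03)
- one endpoint, 4 cohorts: 1 − 0.9895⁴ = 0.041
- two endpoints, 3 cohorts: 1 − 0.9895⁶ = 0.061
- two endpoints, 4 cohorts: 1 − 0.9895⁸ = 0.081

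Simulation at zero correlation gives 0.031, 0.041, 0.062 and 0.080. The second endpoint, more than the missing look, carries the figure past 5%.

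**Step 3: the rule as written, no change, CV 20%, correlation 0.8 to 0.**

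| How a 20% improvement is scaled | Through 9 | Through 12 |
|---|---|---|
| Same log ratio, ln 1.2, for both endpoints | 5.1–6.1% | 6.8–8.1% |
| VI as a 20% fall, −ln 0.8 = 0.223 | 3.7–4.2% | 4.9–5.6% |
| Raw scale, SD 0.20, threshold 0.20 | 3.7–4.4% | 4.9–5.7% |

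**Step 4: the other figures, CV 20%, correlation 0.7 to 0, across these scalings.**

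| True change | Stated | Rule as written |
|---|---|---|
| 10%, by 12 patients | 0.19 | 0.30–0.41 |
| 20%, by 12 patients | 0.58 | 0.77–0.85 |
| 30%, after 6 patients | 0.60 | 0.83–0.96 |

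**Step 5: sensitivity to CV 25%.** With no change, the rule as written gives about 11–16% through 12 patients.

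**The case against.** The strongest defence is that the under-5% sentence may be true on its natural reading. It speaks of an interim time point, the next sentence illustrates this with 6 and 9 patients, and after 12 all treated patients are in. Through 9 patients the full rule gives 3.7–4.4% on the raw scale or with VI as a 20% fall. Only the common log ratio exceeds 5%, and for VI a ratio of 1.2 is a fall of 1 − 1/1.2 = 16.7%, short of the 20% target. This stands: a reader might infer that the under-5% claim is simply false, and the protocol does not support that. It is not assured, because the answer turns on a correlation and a VI scaling that the protocol does not fix.

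Three further points stand.

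- The table is labelled as per endpoint and CV 20%, so its entries are not wrong. The fault is in the sentences that use them as declaration probabilities.
- The 11–16% at CV 25% contradicts nothing, since no interim claim is made for that CV.
- The declaration is for planning a further trial, and both thresholds are given as examples. The termination criteria in section 10 list no stop for success, and section 4 leaves dose decisions to the TSC after DSMB review. It would be wrong to read this as inflation of a confirmatory type I error.

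The defence does not reach the rows for 10%, 20% and 30%. There the gap is 0.11 or more under every scaling and correlation in the stated range.

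**Conclusion.** The point holds at moderate weight. The two sentences under the table report single-endpoint probabilities, with looks from 6 patients and CV 20%, as the probability of declaring efficacy under a rule that uses either endpoint and looks after every cohort. With no change, the rule gives about 5–8% through 12 patients, with the lower end marginal, and 3.7–6.1% through 9. The larger misstatement is for true changes of 10% to 30%: a true 10% change triggers a declaration roughly 1.6 to 2.2 times as often as the table's 0.19 suggests (0.30/0.19 to 0.41/0.19). The ranges rest on the assumed endpoint correlation, equal CV for both endpoints and the three scalings shown. The effect is on how the planning signal is read; no treatment decision or primary analysis follows from it.

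**What to change.** Simulate the complete rule: either endpoint, cohort or pooled, looks after 3, 6, 9 and 12. State the assumed correlation (or a range) and how a 20% VI improvement is defined. Say whether the look after 12 counts as interim. Replace the under-5% and 60% (81%) sentences with the results. Keep the present table, labelled as single endpoint, looks from 6 patients, CV 20%. Add CV 25%, the alternative used in the power table, as a sensitivity.

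The cost is one simulation, a change of wording and a less favourable stated error rate. The individual-cohort clause need not go. Pooled-only testing gets under 1% at CV 20% with no change only if the look after 3 patients is also dropped; kept, it gives about 2%. It also costs detection: for one endpoint at a true 30%, pooled looks from 6 give about 0.55, 0.70 and 0.78, against the table's 0.60, 0.81 and 0.90.
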